## Abstract

**Background:**

Structured psychotherapy is recommended as the preferred treatment of personality disorders. A substantial group of patients, however, has no access to these therapies or does not benefit. For those patients who have no (longer) access to psychotherapy a Collaborative Care Program (CCP) is developed. Collaborative Care originated in somatic health care to increase shared decision making and to enhance self management skills of chronic patients. Nurses have a prominent position in CCP's as they are responsible for optimal continuity and coordination of care. The aim of the CCP is to improve quality of life and self management skills, and reduce destructive behaviour and other manifestations of the personality disorder.

**Methods/design:**

Quantitative and qualitative data are combined in a comparative multiple case study. This makes it possible to test the feasibility of the CCP, and also provides insight into the preliminary outcomes of CCP. Two treatment conditions will be compared, one in which the CCP is provided, the other in which Care as Usual is offered. In both conditions 16 patients will be included. The perspectives of patients, their informal carers and nurses are integrated in this study. Data (questionnaires, documents, and interviews) will be collected among these three groups of participants. The process of treatment and care within both research conditions is described with qualitative research methods. Additional quantitative data provide insight in the preliminary results of the CCP compared to CAU. With a stepped analysis plan the 'black box' of the application of the program will be revealed in order to understand which characteristics and influencing factors are indicative for positive or negative outcomes.

**Discussion:**

The present study is, as to the best of our knowledge, the first to examine Collaborative Care for patients with severe personality disorders receiving outpatient mental health care. With the chosen design we want to examine how and which elements of the CC Program could contribute to a better quality of life for the patients.

**Trial registration:**

Netherlands Trial Register (NTR): NTR2763

## Background

A personality disorder is a severe and complex psychiatric illness. The borderline personality disorder (BPD) and the personality disorder not otherwise specified (NOS) both belong to the two most prevalent personality disorders. The lifetime prevalence of borderline personality disorders is estimated at 1-2% in the general population, whereas in patient samples the prevalence is approximate 10-20%. The personality disorder NOS has an estimated prevalence of 8-13% in patient samples [1,2].

Structured psychotherapy is recommended as the preferred treatment of personality disorders. Several studies report modest positive treatment results [3-9]. Psychotherapy contributes to higher quality of life, reduced psychopathology and destructive behaviour, and sustainable changes in personality.

A substantial group of patients, however, does not benefit from these psychotherapies [10-13]. Besides limitations in availability of these therapies, some patients do not meet the inclusion criteria or they drop out during treatment. Others need more psychosocial support for their many complex social problems. Most patients who do not benefit have a chronic and unstable course of illness with disruptive and destructive behaviour [10,13,14]. They put a high demand on the health care services provided for rather long, but often discontinuous periods of time [15]. These patients often receive community mental health care (often referred to as a team: CMHC team), mostly provided by (community) mental health nurses [10,14]. The treatment delivered by CMCH teams is, however, not standardized and highly unstructured [16,17].

Research indicates that especially nurses in particular experience caring for people with severe (borderline) personality disorders as highly stressful [18-21]. Strong emotional responses towards the patient arise frequently, particularly when the disruptive behaviour of the patient is unpredictable and difficult to understand. This contributes to condemnation of the patient by the nurse and a less empathic attitude. Ambivalent care seeking of these patients, shifting between dependency from and condemnation of professionals, can be explained out of their disorder and the irregular course of the therapeutic process. This same ambivalent care seeking, however, is difficult for care providers to accept and to cope with and it often leads to ineffective professional behaviour [22,23]. On the one hand, while balancing between autonomy and safety of the patient, nurses easily feel forced and responsible to protect the patient. Nurses may apply restrictive interventions to control the patient's destructive behaviour [24-26]. On the other hand, nurses may underestimate the needs and disabilities of their patients and perceive them as able but unwilling to change [27,28]. To keep the balance between playing a waiting game on the one hand, and being overly supportive and protective on the other hand is considered to be difficult with regard to these patients [13,27]. Studies reveal that patients and care providers set different priorities during treatment, including the specific needs of patients that require attention [29-33]. These, at times, conflicting priorities can cause miscommunication between patients and care providers and, hence, adversely affect outcomes of care [29,31].

As a response to these challenges, we developed a structured easily accessible intervention program for this subpopulation of patients, provided by (community) mental health nurses. For this intervention program we have adapted the principles of Collaborative Care (CC) [34-36]. Collaborative Care Programs originated in somatic health care to increase shared decision making and to enhance self management skills of chronic patients. Collaborative relationships come into existence when patients, their informal carers, and care providers have shared goals and mutual understanding of roles, expectations and responsibilities. As a consequence of more effective self management, patients report that their quality of life improves, because they feel they can better cope with problems derived from their disorder [35,36]. To date, Collaborative Care Programs (CCP) have proven to be effective for depressive and bipolar disorders [37-45].

Nurses have a prominent position in Collaborative Care Programs as they function as collaborative care managers. In this position they are responsible for optimal continuity and coordination of care. To optimize the continuity and coordination of care, intensive partnership working is needed within a *Collaborative Care team *(CCT). The CCT consists of the patient, his/her informal carer, the nurse, and the psychiatrist and/or psychologist. The CCT can optionally be expanded with others who possibly could contribute to effective treatment and care of the patient. The CCT lends support to the patient and it is in this team that crucial decisions regarding treatment will be made.

A Collaborative Care Program for patients with severe personality disorder has as to the best of our knowledge not yet been developed or tested. In this stage of intervention development, insights in both the feasibility and as well as the preliminary results of the intervention are needed. Therefore, we combine quantitative and qualitative data in a comparative multiple case study, which makes it possible to test the feasibility of the CCP in clinical practice, and also provides insight into the preliminary outcomes of CCP [46,47]. This study functions as a pre stage for a future RCT. The following research objectives are formulated:

(1). To describe the processes of the application of a Collaborative Care Program for patients with a severe borderline or NOS personality disorder in comparison with Care as Usual (CAU) from the perspective of patients, their informal carers and nurses;

(2). To describe the preliminary outcomes of the CCP in comparison with Care as Usual;

(3). To explain which characteristics of the CCP are indicative for the occurrence of positive or negative outcomes compared to CAU.

## Methods/Design

### Design

A comparative multiple case study may be used for the thorough evaluation of complex intervention programs [46-48]. The research generates descriptive and explanatory data regarding treatment processes and outcomes of the intervention program. Different perspectives are integrated in the evaluation: the perspective of patients, their informal carers and nurses. In our multiple case study two treatment conditions will be compared: one functions as the experimental condition in which the Collaborative Care Program is provided; the other condition functions as the control condition in which Care as Usual (CAU) is offered. Different types of data collection will be used: questionnaires, documents, and interviews. A case is defined as the treatment process of one patient in which integrated data from the three perspectives (patient, informal carers and nurse) concerning the application and the outcomes of the CCP or CAU will be gathered and analysed.

Within a comparative multiple case study, data are analyzed at the individual case level, group level, as well as between groups level [46-48]. The process of treatment and care within both research conditions is described with qualitative research methods. Additional quantitative data provide insight in the preliminary results of the CCP compared to CAU. By means of data triangulation, the connection between the application and the preliminary outcomes of the Collaborative Care Program will be explained in comparison with Care as Usual. With a stepped analysis plan the 'black box' of the application of the intervention program will be revealed in order to understand which characteristics and influencing factors are indicative for positive or negative outcomes.

### Participants

#### Patients

Participants are recruited from two comparable community mental health care (CMHC) teams of a large mental health organisation in the Netherlands. One team is indicated as the experimental condition and the other as the control condition.

Both CMHC teams provide long-term outpatient care for patients with various severe mental disorders. Patients that will be included should be between 18 and 65 years of age, have a main diagnosis of borderline or NOS personality disorder (DSM-IV-TR), have a score of 15 or higher on the Borderline Personality Disorder Severity Index (BPDSI, range 0-90) [5,49] and have received psychiatric care for at least two years. Participants are required to speak and read Dutch sufficiently well to fill in the questionnaires.

Participants are excluded when they currently participate in a structured psychotherapeutic program or when it is expected they will participate in such a program within a period of nine months from the start of the study. All participants will be asked to sign for informed consent based on oral and written information about the research project.

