##### 1. Organization and contracting

A Collaborative Care Team will be put together for adequate coordination of care, with optimal collaboration between the main team partners: i.e. the patient, his/her informal carer(s), a psychiatric nurse and a psychiatrist and/or psychologist. Because discontinuity of care increases the risk of drop-out and a negative course of the psychiatric illness (with possible suicide as the extreme negative outcome), Collaborative Care demands pro-active collaboration between all partners to minimize this discontinuity of care. The nurse is responsible to inform and involve all those partners, whenever necessary. The execution stage of the CCP should not start before a treatment plan is established to which all collaborative partners commit [37,40,42]. Due to the ambivalent care seeking of most of the patients, this stage is therefore crucial and requires a careful preparation. This preparation stage consists of several activities (see Additional File 1).

Within Collaborative Care the patient is perceived as the one who shapes his own life, and hence his own treatment. Active involvement of the patient is required to reach the objectives of improved self management skills and shared decision making [36]. Patients, however, often have a long history of contacts with health care providers, with divergent success. To learn from previous experiences, an inventory is made of life events and of former treatments, based on the medical record. This inventory will be discussed with the patient and with the other members of the Collaborative Care Team to identify effective coping strategies with life events, effective elements in treatment, and relationships. Patients are invited to express their expectations about care providers and treatment and to speak aloud about disappointing (sometimes even traumatic) experiences, which still may hamper the relationships with care providers. Informal carers are invited to share their view upon past life events and expectations with regard to collaboration and treatment. Mutual expectations and responsibilities are made explicit between patients, informal carers and care providers, in order to promote a strong relationship [26,50]. The agreements about the collaboration are recorded in the treatment plan.

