### Control Condition

Patients in the control condition receive care as usual from their current care providers. During the study period, nurses in both conditions are not permitted to receive any extra training that might interfere with the content of the CCP.

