#### Data collection

There are three measurements in this study: when participants enter the study (T0), after five months (T1) and after nine months (T2). To achieve the formulated objectives of this study, the data collection is divided into two parts. Quantitative data are collected with questionnaires to describe the outcomes of the CC Program in comparison with the CAU (summarized in table 1). Qualitative data, such as interviews, and records of the supervision sessions are used to analyse the implementation process of the application of the CCP in comparison with CAU. Data will be collected among patients, their informal carers and nurses, as mentioned below.

**Table 1 T1:** Summary of the used questionnaires.

	Questionnaires		
Outcome indicator	*Patients*	*Informal caregivers*	*Nurses*
Quality of Life	▪ Manchester Short Appraisal (MANSA)		
Psychopathology	▪ Borderline Personality Disorder Severity Index (BPDSI) ▪ Structured Clinical Interview for DSM-IV Personality Disorders (SCID-II)		
Destructive behaviours	▪ BPDSI ▪ Beck Scale for Suicide Ideation (BSSI) ▪ CAGE questions-adapted to include drugs (CAGE-AID)		▪ Suicide Behaviour Attitude Questionnaire (SBAQ) ▪ Attitudes Towards Deliberate Self-Harm Questionnaire (ADSHQ)
Health care use	▪ Trimbos/iMTA questionnaire for Costs associated with Psychiatric Illness (Tic-P)		▪ process forms
Psychosocial symptoms	▪ Brief Symptom Inventory (BSI)		
Satisfaction	▪ Consumer Quality-index (CQ-index)	▪ CQ-index	
Therapeutic Alliance	▪ *S*cale *t*o *A*sses Therapeutic *R*elationships in Community Mental Health Care (STAR)		▪ STAR
Mastery	▪ Pearlin Mastery Scale (PMS)		
Involvement/social support		▪ Involvement Evaluation Questionnaire (IEQ)	

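### Condition is fixed by existing team and can be known during recruitment, with no safeguard described, so consenting patients may differ between conditions before treatment starts

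*Protocol article*

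**What the plan says.** **Source of patients and assignment.** In the protocol article, under Participants, Patients: "Participants are recruited from two comparable community mental health care (CMHC) teams of a large mental health organisation in the Netherlands", and "One team is indicated as the experimental condition and the other as the control condition". No randomisation and no concealment of condition is described. The Nurses section likewise includes nurses by condition, ten experimental and five control, on a voluntary basis.

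**Eligibility.** The criteria are the same for both conditions. They include the requirement to "have a score of 15 or higher on the Borderline Personality Disorder Severity Index (BPDSI, range 0-90". Current participation in structured psychotherapy excludes a patient, and so does expected participation within nine months. No criterion concerns motivation.

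**Consent and baseline.** One sentence covers consent: "All participants will be asked to sign for informed consent based on oral and written information about the research project". Measurements are taken "when participants enter the study (T0), after five months (T1) and after nine months (T2", so baseline falls at individual entry.

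**What each condition asks of patients.** For CCP, the section on organization and contracting says "Active involvement of the patient is required to reach the objectives of improved self management skills and shared decision making", and "The execution stage of the CCP should not start before a treatment plan is established to which all collaborative partners commit". It calls this stage crucial because most of these patients seek care ambivalently. Under Control Condition: "Patients in the control condition receive care as usual from their current care providers".

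**Use of the comparison.** The Data analysis section compares the conditions to judge the value of CCP against CAU. The Quantitative analyses section calls the results preliminary and supportive of the qualitative data. The Discussion places the study before the question of effectiveness.

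**The concern.** When condition is tied to the team and can be known at recruitment, it can influence three decisions: whom the team approaches, how the forward-looking psychotherapy exclusion is judged, and who agrees to take part. CCP and CAU place very different demands on patients, and the protocol itself treats ambivalence about care as central to this population. Differences in readiness to collaborate, or in severity, could therefore enter at recruitment.

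This is distinct from pre-existing differences between the teams. It could operate even if the two caseloads were identical, so describing the teams as comparable does not answer it.

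What is at stake is the comparison of conditions and the third research objective, which seeks to explain outcomes by characteristics of CCP. Readiness to collaborate would be a rival explanation, and the findings are to be used to adapt the program for a later RCT.

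**Working it through.** **1. The plan's own figure.** At least 16 patients in each of two conditions gives 2 × 16 = 32 cases, as stated under Selection of patients. That section calls the required number arbitrary and gives no effect size, SD or power, so there is no power calculation to check.

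**2. The passages side by side.**

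| Step | What the article states | What it leaves open |
|---|---|---|
| Assignment | Whole team, one per condition | Whether this precedes recruitment, and who is told when |
| Eligibility | Same criteria, one of them a judgement about expected psychotherapy | Whether that judgement is made without regard to condition |
| Consent | One sentence for all participants, about the research project | Whether patients know their team's condition when they sign |
| Baseline | At study entry | Whether T0 precedes disclosure of condition |
| Demands | CCP: involvement and commitment; CAU: unchanged care | Whether willingness to take part differs as a result |

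The first and last rows make condition-aware recruitment possible and relevant. Nothing in the article closes the route, and nothing shows that it was taken.

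**3. Possible size (illustration only).** Neither input is in the documents. Let p be the difference between conditions in the share of readily collaborating patients, assumed to be 0.10 to 0.30. Let d be the extra improvement of such patients whatever care they receive, assumed to be 0.3 to 0.8 SD. The spurious difference is b = p × d.

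- Lower: 0.10 × 0.3 = 0.03 SD
- Upper: 0.30 × 0.8 = 0.24 SD

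The sign of p is not known. The same arithmetic with p reversed gives −0.03 to −0.24 SD, and p = 0 gives none.

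**4. Scale against sampling error.** With 16 per condition and unit SD, the standard error of a difference in means is √(2/16) = 0.35 SD. The whole assumed range is below one standard error.

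**5. Effect on a two-sided 5% test when there is no treatment effect.** By normal approximation, ignoring clustering by team and nurse, the rejection rate is Φ(b/0.354 − 1.96) + Φ(−b/0.354 − 1.96).

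| Assumed b (SD) | Rejection rate |
|---|---|
| 0 | 5.0% |
| 0.2 | 8.7% |
| 0.3 | 13.6% |
| 0.5 | 29.3% |
| 0.8 | 61.9% |

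For b = 0.2: 0.2/0.354 = 0.57, and Φ(−1.39) + Φ(−2.53) = 0.082 + 0.006, about 0.087 before rounding of the parts. The last three rows lie above the range in step 3 and only show how the rate grows. The rate is the same for a bias of either sign.

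**The case against.** A reader might infer that CCP patients consent to a contracting programme, that CAU patients consent only to measurement, and that more motivated patients are therefore selected into CCP. The documents do not support this. There is one consent sentence for all participants. It does not say that the information differs by condition or that patients know their condition. Contracting and commitment to the treatment plan belong to the preparation stage of the intervention and are not stated as conditions of consent. That stage is designed to work with ambivalent patients. CAU patients also agree to interviews and may allow a carer to be approached. No data on refusal or motivation are given, and a low-burden study with unchanged care could attract a different kind of willing patient. The direction is therefore open.

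Other objections carry weight:

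- **Condensed article.** The approach procedure and information letter may be set out in the full protocol. The absence of detail is not itself a fault. What stands is that the article fixes the design feature that makes a safeguard necessary. If the full protocol already contains one, the point is met.
- **Baseline proxies.** The patient-rated therapeutic relationship (STAR) and mastery scales are partial proxies for readiness, so baseline adjustment can remove some of a difference. Neither measures readiness directly.
- **Declared limits.** The study is presented as a preliminary stage before an RCT. This lowers the weight of the point. It does not remove it, because the conditions are still compared to judge the value of CCP.
- **Feasibility.** It does not follow that feasibility is biased towards CCP. The article defines no uptake endpoint, and a later RCT would also enrol only consenting patients.
- **Limits of the remedy.** Delayed disclosure may move refusal to after disclosure, mainly in the CCP team. That is true, but such refusals would then be visible and accompanied by T0 data.

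**Conclusion.** The point holds as a risk. Condition is assigned by existing team and can be known to recruiters, and possibly to patients, at eligibility assessment, consent and T0, with no safeguard described. Because the two conditions ask such different things of patients, those who consent may differ in readiness to collaborate or in severity. That CCP is favoured is plausible but not established.

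The size is unknown. The 0.03 to 0.24 SD range rests wholly on assumed inputs, could have either sign, and is small against a standard error of 0.35 SD. At 0.2 SD it would raise the false-positive rate from 5% to about 9%, in analyses described as preliminary. The change is worth making because it is inexpensive and because the results will shape a later RCT.

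**What to change.** 1. In both teams, list all eligible patients from the full caseload by the same criteria, including the judgement on expected psychotherapy, before anyone is approached.
2. Approach them in the same way in both teams, with one information letter that describes both conditions.
3. Where feasible, complete consent and T0 before patients are told their team's condition and before CCP starts.
4. Report the numbers listed, approached, refusing and consenting per team, and count separately any who withdraw after disclosure.
5. Compare T0 characteristics between conditions, and use baseline-adjusted comparisons of outcomes.
6. State in the article that these steps do not separate a team effect from the CCP effect, because there is only one team per condition.

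**Cost.** Some weeks' delay to the nurse training and the start of CCP, and ethics review of the amended letter. No extra patients or measurements are needed. If delayed disclosure proves impracticable, steps 1, 2 and 4 still let readers judge how far recruitment differed between the teams.
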